## Abstract

Background: given the limited efficacy, tolerability, and accessibility of pharmacological treatments for chronic migraine (CM), new complementary strategies have gained increasing attention. Body ownership illusions have been proposed as a non-pharmacological strategy for pain relief. Here, we illustrate the protocol for evaluating the efficacy in decreasing pain perception of the enfacement illusion of a happy face observed through an immersive virtual reality (VR) system in CM. Method: the study is a double-blind randomized controlled trial with two arms, involving 100 female CM patients assigned to the experimental group or the control group. The experimental group will be exposed to the enfacement illusion, whereas the control group will be exposed to a pleasant immersive virtual environment. Both arms of the trial will consist in three VR sessions (20 min each). At the baseline and at the end of the intervention, the patients will fill in questionnaires based on behavioral measures related to their emotional and psychological state and their body satisfaction. Before and after each VR session, the level of pain, the body image perception, and the affective state will be assessed. Discussion: this study will provide knowledge regarding the relationship between internal body representation and pain perception, supporting the effectiveness of the enfacement illusion as a cognitive behavioral intervention in CM.

## 1. Introduction

Migraine is known as one of the most prevalent and disabling neurological disorders worldwide [1]. Usually, it recurs in an episodic pattern (less than 15 days/month—episodic migraine), but in a small, though clinically relevant portion of sufferers, migraine may acquire an aggressive evolution being present on 15 or more days/month. This is so-called chronic migraine (CM) [2]. CM is mainly managed through pharmacological treatment, requiring both the acute drugs taken during attacks and the preventive treatment aimed at reducing the frequency of attacks [3]. Unfortunately, available treatment options have limited efficacy (50% reduction of migraine days in 50% of patients), they may be poorly tolerated, and they can induce clinically relevant side effects [4,5]. In addition, when considering that CM is a complex neurological disorder that may manifest with variable phenotypical profiles and response to treatments, it is important to tailor the treatment approach to patient’s characteristics and inter-individual differences. In this regard, it should be noted that CM is often associated with several comorbidities [6], including those of a psychological nature, such as dependence behaviors, anxiety, depression, and personality disorders [7,8,9,10,11,12], which could affect the course of treatment [7,8]. As consequence, persistent pain associated to CM poses a high socio-economic burden [13,14], including the costs of pharmacological treatments, primary care visits, and hospitalizations, together with the impact on the patient’s productivity and everyday life [14,15]. Because of this, recent years have seen a proliferation of new therapeutic strategies to address migraine-related pain, as well as new techniques that offer promising approaches for development that could be integrated into pharmacological options.

Nowadays there is an increasing interest in the integration of new technologies for clinical practices [16]. In particular, virtual reality (VR) has been widely used to promote mental health in populations presenting different clinical conditions [17]. Recently, several investigations showed the effectiveness of a VR-based approach for pain relief in patients suffering from chronic pain [18,19,20]. Indeed, VR has been shown as being effective as a treatment strategy for burn pain, acute pain, or induced pain [21,22,23,24,25,26]. VR as an analgesic option that can be used in two modalities: as a distraction therapy through immersiveness, and as a tool for modulating body representation through virtual body ownership illusions (BOI) [18,24,27,28]. Distraction therapy consists in temporally diverting the patient’s attention from the pain through the VR experience [29]. In detail, the cognitive mechanisms that mediate VR-based interventions as a distraction therapy for pain relief are attention, concentration, and emotional alteration [30]. Moreover, the immersiveness on such VR environments allows participants to fully interact with the environment increasing the distraction from pain [28,31,32].

The use of virtual body ownership illusions for pain relief relies on inducing the sense of embodiment toward virtual bodies for changing body representation [33,34]. The sense of “embodiment” refers to the sense of having a body [35] and it is the result of a complex interaction between bottom-up and top-down sensory information [36]. According to this, the sense of embodiment consists in three subcomponents: the sense of self-location, the sense of agency, and the sense of body ownership [33]. Once embodiment is successfully induced, the subject feels as though they are inside a body that is moving according to his/her own intentions and interacting with the environment [33]. In the last few years, there has been a proliferation of studies trying to understand how to experimentally manipulate bodily perception and embodiment by using virtual body ownership illusions [37,38]. This is possible because a main feature of the VR system is its capability to induce a sense of ‘presence’, that is the sense of ‘being there’ within the virtual environment [39,40,41]. According to this, a large number of studies have tested virtual body ownership illusions by using synchronous visuo-tactile or visuo-motor correlations for inducing the sense of embodiment in a VR environment where participants could feel fully immersed into and present in the generated virtual world. [42,43,44,45]. In this regard, it has been demonstrated that watching the face of another person while that face and one’s own face are stroked synchronously induces the illusion of self-recognition toward the other face, the so-called “enfacement illusion” [46,47].

The enfacement illusion is the result of the plasticity of the self-face representation, which can be temporarily modified to include another person’s facial features [46,47]. Hence, the enfacement illusion has resulted as a good strategy for changing self-representation, with important implications for all those subjects who have distorted body representations, including patients suffering from chronic pain [48,49,50]. Indeed, a recent study showed that it is possible to induce the enfacement illusion by using VR systems [51]. The enfacement illusion is associated with improved emotional contagion and emotional recognition. It has indeed demonstrated that there is a sort of “mood migration” from the virtual face to another person’s face in case of synchronicity between them [52]. In line with this point, a recent study [53] has shown that by applying synchronous visuo–tactile stimulation observed through videos, it is possible to boost facial mimicry, which is the automatic imitation of another person’s emotion. From a neuroimaging point of view, the virtual experience derived from the enfacement illusion is able to induce changes in the sensory–motor cortex [54], and in particular in those areas that are the neural basis of body image [55] and emotion processing [56,57,58], that is, the primary sensory (S1) and motor (M1) cortices. Interestingly, these brain areas are involved in the cerebral dimensions of pain: one representing the discriminative dimension (S1) and one representing the affective dimension (M1).

It has been indeed shown that the perception of pain can alter both facial recognition and visuospatial perception in CM compared to healthy subjects [59]. Furthermore, it has been found that by reducing the altered perception of body image in CM patients with medication overuse, it is possible to induce beneficial effects on their affective state and on their perception of pain [60]. Moreover, there is evidence that electrophysiological homeostasis is altered abnormally (allostatic load) in a migraine brain with regard to what concerns sensory–motor network interactions [61,62,63,64,65] as well as neurostimulation techniques applied at the right M1 or S1 which can effectively decrease migraine pain frequency, duration, and intensity [66]. Recently our research group has evaluated the effects of an intervention based on visual feedback—i.e., intended to modify pain through the perception of the body image by means of the observation of facial expressions with different emotional content [67]—on the modulation of pain perception in a sample of female CM patients [68]. Interestingly, we showed that the simple observation of a facial expression with positive emotional content, when compared to other emotional content (negative or neutral), was able to decrease pain perception. The results from this study have paved the way for the integration of new technologies, such as VR systems, for modulating body representation through the use of virtual body ownership illusions, in particular through the use of the ‘enfacement illusion’. To the best of our knowledge, no study has used the enfacement illusion for the treatment of pain in patients suffering from CM.

The present study protocol presents a longitudinal randomized controlled trial (RCT) protocol, which aims to investigate whether it is possible to decrease pain perception in patients with CM by inducing the enfacement illusion of representing oneself in a happy face through a VR system (experimental group). It is expected that this effect is mediated by an improved body image perception and empathy for positive emotions. Our previous findings [68] allowed us to explore the different effects of being exposed to neutral or sad stimuli. Hence, in the present study, we used the positive emotional face as being the only one recognized as effective for pain relief in patients with CM. According to this, the main aim of this study is to enucleate specifically the effect of enfacement from the possible synergic effect of the exposure to a positive stimulus (happy face). In the control group, the patients will be subjected to a positive exposure (pleasant environment) in an immersive VR environment, which has already been demonstrated to be able to produce distracting effects on pain perception in patients with CM [69]. The rationale for choosing this control condition derives from the willingness to use another positive visual stimulus in immersive VR, which is already known to be effective in distracting individuals from pain in CM [69], that can serve to appreciate the additional effects of producing the enfacement illusion of a happy face in the experimental group. It is hypothesized that patients in the experimental group will experience greater pain relief and will improve the perception of their body image compared to the control group. Therefore, the present protocol study aims to show a possible relationship between the manipulation of the body image and pain perception and to demonstrate the effectiveness of the use of the virtual enfacement illusion as a cognitive behavioral intervention for pain relief in CM.

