## 2. Materials and Methods

### 2.1. Study Design

The proposed study is a prospective double-blind RCT with two arms. A CONSORT flow chart for enrollment and randomization is shown in Figure 1. Patients fulfilling inclusion criteria, once they have signed the informed consent form, will undergo a baseline assessment (T0) using the below-listed tests and will be randomized to one of two groups: experimental and control. Both groups will be exposed to three VR sessions each lasting approximately 20 min during a one-week period. The first session will be carried out immediately after enrollment and T0, whereas the next two will be carried out in the following days when the patients will report to have a migraine attack. At T0 and at the end of the intervention (T1), the patients will fill in a questionnaire based on behavioral measures related to their emotional and psychological state and their body image perception. T1 assessment will then be carried out at the end of the last VR session. Before and after each VR session the level of pain, body image, and affective state of the patients will be assessed. Furthermore, after each VR session, the sense of embodiment (experimental group) or the sense of immersiveness (control group) will be assessed.

This study protocol conforms to the Standard Protocol Items: Recommendations for Interventional Trials (SPIRIT) guidelines (see Supplementary Table S1).

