#### 2.8.1. Experimental Group

Patients in the experimental group will be exposed to the enfacement illusion condition, conducted similarly to other studies in other fields of research [47] (Figure 3 and Figure 4). In detail, patients will see, through the HMD, a virtual body sitting in front of them in the same position showing a happy face expression. Each session will consist of four phases:(1)Observation of the virtual facial expression and habituation to the virtual environment: the experimenter will ask patients to focus their attention on the face of the virtual body sitting in front of them for about one minute.(2)Visuo–tactile stimulation: in order to induce the enfacement illusion in the patients, the experimenter will use a brush to apply synchronous visuo–tactile stimulation to the real face of the patients, while they will be observing a synchronous tactile stimulation on the happy face displayed in the 360° video equally applied by the experimenter in the same place and at the same time. The synchronous visuo–tactile stimulation will be applied for 2 min.(3)The observation of the virtual facial expression and habituation to the virtual environment phase will be repeated to update habituation to the virtual environment.(4)The synchronous visuo–tactile stimulation phase will be repeated to update the induction of the enfacement illusion.

Overall, the patients will receive 4 min of synchronous visuo–tactile stimulation to induce the enfacement illusion to the happy face displayed in the 360° video through the HMD. The synchronous stimulation will be recorded with a metronome sound (60 beats per minute) in the 360° video. During the experimental session, the researcher will stimulate the face of the patients which at the same time will be synchronized with the beat sound displayed in the video. Patients will observe the same situation when they are immersed into the 360° virtual scenario: a researcher stimulating the virtual face placed in front of them. A beep sound will indicate the experimenter wants to start the stimulation, and he/she will follow the sound of the metronome for each stimulation. After exposure to the 360° video, the patients will fill in a questionnaire regarding the induction of the ‘enfacement illusion’ adapted from [77].

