#### 2.8.2. Control Group

Participants in the control group will be exposed to a visual stimulation by observing a pleasant immersive virtual reality environment [69] (Figure 5 and Figure 6). As in the experimental group, there will be two minutes for the habituation to the virtual environment, where the experimenter will ask the patients to describe what they see. Then, the patients will observe the pleasant virtual environment for about 4 min.

After immersion into the virtual environment, the patients will fill in a questionnaire regarding the virtual reality experience adapted from [39].

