## 3. Discussion and Conclusions

CM represents a life-altering condition resulting in a significant reduction in the quality of life [81]. Sufferers are usually treated with acute medications and preventive treatments, which can be poorly tolerated and present significant risks and side effects [4,5,82]. Hence, CM patients are left with few efficacious and safe therapeutic options. To this end, the technological advancements of the last few years are providing promising and novel non-pharmacological options to be adopted for treating clinical conditions, including pain states. VR systems aimed at reducing virtual BOIs can then represent new tools for the study of perceptual processes acting on body ownership [17,26] and emotional states [52,53]. In this field, synchronous multisensory stimulations, such as visuo–tactile stimulation, can be used temporarily to induce enfacement, which is the subjective illusion of ownership of another person’s face [46,47]. The experimental induction of the enfacement illusion can represent an interesting application strategy for pain relief in CM.

The present RCT will provide evidence about the use of the enfacement illusion in virtual reality for pain relief in CM. It is expected that such results will arise because of the improvement in body image perception and empathy for positive emotions. Results of this RCT will advance the knowledge of this painful condition by exploring the relationship existing between internal body representation, distortion of the body image, and pain perception in CM. Furthermore, the results from this study will support the effectiveness of body ownership illusions, such as the use of the enfacement illusion, as a cognitive behavioral intervention for pain relief.

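### The stated main aim is to isolate enfacement from the happy face, but the two-arm contrast supports only a comparison of the whole package with a pleasant VR scene

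*Protocol article*

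**What the plan says.** All references are to the protocol article.

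- **Aim (Introduction, last paragraph).** "the main aim of this study is to enucleate specifically the effect of enfacement from the possible synergic effect", and the sentence continues "of the exposure to a positive stimulus (happy face". The element to be separated out is therefore named: the happy face.
- **Design (Section 2.1).** "The proposed study is a prospective double-blind RCT with two arms". The primary analysis in Section 2.12.2 is a one-factor ANOVA (or its rank equivalent) with group as the only factor, followed by mixed models across sessions.
- **Experimental arm (Section 2.8.1).** Patients see "a virtual body sitting in front of them in the same position showing a happy face expression". Then "the experimenter will use a brush to apply synchronous" visuo-tactile stimulation to the patient's real face, timed by a metronome, in two periods of 2 minutes.
- **Control arm (Section 2.8.2).** Patients are "exposed to a visual stimulation by observing a pleasant immersive virtual reality environment". No face, no touch and no asynchronous condition is described.
- **The team's previous study (Introduction).** The team reports that "the simple observation of a facial expression with positive emotional content" lowered pain in female CM patients when compared with negative or neutral content.
- **Illusion check (Section 2.4 and the note to Table 1).** The embodiment questionnaire is for the experimental group only. The control group completes an immersion questionnaire instead.
- **Planned conclusion (Section 3).** "the results from this study will support the effectiveness of body ownership illusions", with the effect ascribed to improved body image and empathy for positive emotions. The Abstract and the end of the Introduction carry the same message about the enfacement illusion.

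**The concern.** To separate enfacement from the happy face, some comparison has to hold the happy face constant while enfacement varies. The protocol contains no such comparison. Every patient who sees the happy face also receives synchronous stroking, and every patient who does not see it receives neither.

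The component left uncontrolled is not incidental. The protocol reports it as active on pain without any illusion, and gives that as the reason for choosing the happy face. If the experimental arm does better, the result could be credited to body ownership when it came from the face or from the touch. The interpretation of the trial's main result is at stake. The Strengths and Limitations section does not mention the problem.

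**Working it through.** **1. Components by arm**

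| Component | Experimental (2.8.1) | Control (2.8.2) |
|---|---|---|
| Immersive VR through the headset | yes | yes |
| Positive visual content in general | yes | yes |
| Same experimenter conducting sessions (2.8) | yes | yes |
| Happy face | yes | no |
| Stroking of the patient's face | yes | no |
| Visuo-tactile synchrony (the enfacement manipulation) | yes | no |
| Pleasant scene | no | yes |

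The described exposure phases have about equal length: 1 + 2 + 1 + 2 = 6 min in the experimental arm and 2 + 4 = 6 min in the control arm. Exposure time is therefore not a further difference on this description.

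**2. What the contrast estimates**

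Write F, T and S for the pain reduction due to the face, the touch and the synchrony (enfacement), and E for that due to the pleasant scene. Assume additivity; interactions would only add unknowns. Then

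experimental minus control = F + T + S − E.

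Two arm means give one equation. Take the planned standardised difference of 0.5:

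- S = 0.5 with F + T − E = 0 fits.
- S = 0.25 with F + T − E = 0.25 fits.
- S = 0 with F + T − E = 0.5 fits.
- If F + T is smaller than E, S exceeds 0.5.

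S is not identified. A larger sample narrows the interval around the sum and leaves S as undetermined as before.

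**3. What the planned sample size powers**

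Section 2.12.1 gives mean changes of −40 and 10, SD 100, one-sided alpha 0.05 and power 80%. So |d| = 50/100 = 0.5, and

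n per group = 2(1.645 + 0.842)²/0.5² = 12.37/0.25 = 49.5, rounded up to 50, total 100.

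The stated figure reproduces, with power 80.4% by the normal approximation. The exact t calculation gives 51 per group, and 79.9% power at 50. This is power for F + T + S − E, not for S.

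**4. Can the embodiment score recover S?**

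It is not collected in the control arm, so the strength of the illusion cannot be compared between arms. A correlation with pain change within the experimental arm is not a randomised comparison.

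**5. What an isolating control would imply (illustration)**

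The share of d = 0.5 due to enfacement is an assumption; the documents give none. Against a control with the same face and touch but without synchrony (one-sided 0.05, 80% power, exact t):

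| Assumed share | d | n per group needed | Power at 50 per group |
|---|---|---|---|
| 100% | 0.5 | 51 | 80% |
| 75% | 0.375 | 89 | 59% |
| 50% | 0.25 | 199 | 34% |
| 25% | 0.125 | 793 | 15% |

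**The case against.** The best defence is that the control was chosen deliberately. Directly after the aim, the Introduction explains that it is another positive visual stimulus in immersive VR, already shown to distract CM patients from pain, so that the added effect of enfacement with a happy face can be seen. The hypothesis in the Introduction and the primary outcome in Section 2.9 are worded as treatment versus control. This stands for the package: immersion and general pleasantness are controlled, and the randomised comparison is valid. It does not rescue the isolation aim, because a pleasant scene does not hold constant the happy face that the aim names.

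A second defence is that stroking is the means of inducing the illusion and so belongs to the treatment. That is fair, and it is a reason not to build the case on a count of differing components. The happy face remains aliased with enfacement even if touch and synchrony are treated as one.

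The study also calls itself a pilot. That bears on the choice of comparator, but it does not justify an attribution that the comparator cannot support.

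A reader might infer more than the documents allow:

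- *That a benefit is to be expected even if enfacement does nothing.* The earlier study compared the happy face with negative and neutral faces, not with a pleasant VR scene, and the control here is described as effective. A difference without enfacement is possible; its sign is unknown.
- *That the plan fails to test a mediation objective.* Mediation is stated only as an expectation, and no mediation test is listed in Sections 2.9 or 2.12.2. Body image (BIQ) and affect (PANAS) are each measured six times. Only empathy has no scale in Table 1.

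**Conclusion.** The point holds for the isolation aim in the Introduction and for the attribution to body ownership in Section 3. The happy face, facial stroking and synchrony are completely aliased in a single group contrast, so the enfacement effect cannot be identified at any sample size. It cannot be bounded as a fraction of the observed difference either, since it exceeds that difference if the face and touch together do less than the pleasant scene.

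It would be too strong to say that the trial cannot answer any of its questions. It can estimate whether the happy-face visuo-tactile VR package relieves pain more than a pleasant VR environment, and the stated 100 patients are calculated for that contrast.

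The conclusion rests on the arms as described in Sections 2.8.1 and 2.8.2. It does not depend on the additivity assumption or on the assumed shares in the power illustration.

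**What to change.** Change the wording; the design can stay.

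1. **Introduction.** Replace the isolation aim with a comparison of pain change after the whole happy-face visuo-tactile VR package, intended to induce enfacement, with pain change after a pleasant VR environment.
2. **Abstract, end of the Introduction and Section 3.** State the conclusions as that package comparison. Remove the attribution to body ownership or to enfacement as such.
3. **Empathy.** Present its role as an untested hypothesis, because Table 1 contains no empathy measure.
4. **Embodiment score.** Its association with pain change within the experimental arm may be reported, labelled exploratory and non-randomised.
5. **Strengths and Limitations.** Add that the face, touch and synchrony effects are not separable in this design.

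The cost is some edits and a narrower claim, with no change to procedures or sample size.

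Keeping the isolation aim would need a happy-face control that differs only in synchrony. That is a design trade-off and not part of this low-cost fix. Substituting it would give up the deliberate comparison with distraction VR, would need a protocol amendment, and could leave 50 per group well short of 80% power unless enfacement carried nearly all of the assumed effect.
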